### Standard care

The intervention is given in addition to standard care. The control group is offered standard care only. Standard care was chosen as the comparator as this is what needs to be improved.

Medication reconciliation is performed by a clinical pharmacist within 24 h of ED admission for all patients [61]. If available, an initial medication list is obtained from the admitting ED physician. This initial list is compared with the hospital’s electronic patient record system and Shared Medication Card, a central containing information about all medications prescribed and dispensed within the previous 2 years [62]. Each participant is then asked to confirm the use of each medication. If a participant is unable to provide reliable information, then the medication list is confirmed with a caregiver (e.g., family member, GP, home nurse, nursing home staff, or community pharmacy). The final medication list is documented in the electronic patient record along with any discrepancies between the initial and final medication list. The final medication list is communicated to the providing geriatrician, who updates the participant’s electronic prescriptions accordingly.

According to the regional nutritional guideline in the Capital Region of Denmark, all patients with an expected hospital stay of more than 24 h should be screened for nutritional risk during the first 24 h of hospitalization and have treatment initiated when relevant [63]. All trial participants are offered the same foods and nutritional products during hospitalization, except for the protein supplement P-Boost®, which is only offered to participants in the intervention group (see the “Dietary Counseling” section).

All municipalities offer food service (paid by the recipient) and home care meal support. None of the municipalities have systematic identification of malnutrition. The municipality of Hvidovre offers home visits from a dietician for citizens who experience unintentional weight loss or declining functional ability or if the municipality is informed of a citizen at risk of malnutrition during hospitalization. The dietician offers unlimited dietary counseling until the goal of counseling is reached, or the counseling is deemed to be unfruitful. The municipality of Copenhagen offers nutritional advice from a nurse to citizens identified as having malnutrition by care staff. The municipality of Brøndby offers dietary counseling from a community-based dietician to citizens with malnutrition who are identified by care staff. Due to the variation between the municipalities, randomization is stratified by the municipality.

### Interventions

The intervention is individualized: participants in the intervention group without malnutrition (MNA-SF >11) only receive the MED intervention, and participants in the intervention group with or at risk of malnutrition (MNA-SF ≤11) receive the MULTI-NUT-MED intervention (see Fig. 1 and Table 1).

#### Medication review intervention (MED intervention)

After the final medication list is obtained and baseline data are available, each participant is given a structured, patient-oriented medication review by the clinical pharmacist. All medications are reviewed to evaluate the (1) agreement with current national guidelines regarding choice of medication, dose, and dosing interval; (2) whether the goal of treatment has been met; (3) presence of nausea, constipation, diarrhea, loss of appetite, or dry mouth related to use of the medication; and (4) whether there is inadequate treatment of any current diagnoses or conditions. PIMs are identified using the Screening Tool of Older Persons’ Prescriptions criteria version 2 [64]. Prescribing recommendations based on eGFR are obtained from Renbase® [65] and “pro.medicin.dk,” a database containing information on national medication and treatment guidelines [66]. Medications are considered “renal risk medications” if dose adjustments are recommended at eGFR ≤90 mL/min/1.73 m^2^. Drug interactions are determined using the national database “interaktionsdatabasen.dk” [67]. Finally, each prescribed medication is assessed for appropriateness based on the indication for treatment, recommended dose, adverse drug reactions, therapeutic duplication, dosing interval, formulation and strength, drug interactions, contraindications, precautions, and specific participant characteristics. The clinical pharmacist documents any recommended changes to the participant’s medication list in the electronic patient record. These recommendations are then reviewed by a geriatrician, who decides whether to accept, reject, or alter each recommendation in collaboration with the clinical pharmacist. Any medication changes made by the geriatrician are documented, in the electronic patient record and implemented in the ED, accepted but not implemented in the ED, communicated to a specialized hospital ward and/or the participant’s GP, or rejected [36].

#### Multidisciplinary nutritional intervention (MULTI-NUT-MED intervention)

In addition to the MED intervention described above, the multidisciplinary nutritional intervention consists of an individualized multimodal and transitional intervention that includes dietary counseling, occupational therapy, physiotherapy, evaluation and treatment of depression, and an oral health-related intervention. The choice of intervention is based on screening tests performed during the baseline data collection (see Figs. 2 and 3).

**Fig. 3 Fig3:**
[figure not shown]
Overview of interventions offered to participants in the intervention group. Details of the screening procedures and interventional content can be found in the section “Medication review intervention” and “Multidisciplinary Nutritional intervention”. Abbreviations; Multidisciplinary (MULTI), Nutritional (NUT), and Medication (MED)

#### Dietary counseling

Dietary counseling is provided both during hospitalization, by research dieticians, and after hospital discharge by community-based dieticians or by hospital-based research dieticians if community-based dieticians are not available. The goal of dietary counseling is to ensure that each participant receives a diet that covers the energy and protein requirements to either maintain their body weight (if BMI≥18.5) or gain body weight (if BMI <18.5). Both the content of the dietary counseling and the structure of the home visits after discharge are inspired by Lindegaard et al. [68, 69].

##### During hospitalization

Immediately after randomization, the research dietitian creates a dietary plan in collaboration with the participant for the participant to follow during hospitalization. This dietary plan is based on foods and nutritional products available at the hospital as well as the participant’s nutritional needs [70], self-reported food preferences, and ability to chew (oral or dental pain and masticatory difficulties) and swallow (evaluated by the EAT-10 score [71, 72] and an occupational therapist).

Foods and nutritional products available at the hospital include a fixed menu in the ED or an *a la carte* menu in specialized wards, energy- and protein-enriched or texture-modified menus, oral nutritional supplements (ONS), and a selection of beverages and in-between meals. Participants in the MULTI-NUT-MED intervention may also receive P-Boost®(Adosan), a fluid protein-only supplement.

Daily dietary intake is recorded in a food diary by the participant and validated by the research dietician the following day. If a food diary is incomplete, then the research dietician performs a 24-h dietary recall [73]. Both dietary intake and dietary plans are entered in VITAKOST [74]. If 100% of energy and protein and energy requirements is not achieved on a given day, then the dietary plan is adjusted for the following day. If >75% of protein and energy requirements is not achieved for 2 days in a row, then tube feeding or parenteral nutrition is advised in collaboration with the medical doctor.

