##### After discharge

Prior to discharge, a dietary plan for the first week after discharge is created based on the participant’s food preferences, nutritional needs (evaluated by the Nordic Nutrition Recommendations [75] with an optional stress factor), ability to chew (pain in their mouth, difficulties chewing) and swallow (evaluated by the EAT-10 score [71, 72] and an occupational therapist), and limitations in grocery shopping, cooking or eating (evaluated by the Functional Recovery Score (FRS) [76]). If ONS is a part of the dietary plan after discharge, then the participant is provided with an ONS prescription, which can be filled at the pharmacy with a 60% price reduction. At discharge, the dietary plan is provided to both the participant and community-based dietician.

Participants are offered 1-h home visits by the community-based dietician at 1, 2, 4, and 8 weeks after discharge to evaluate changes in body weight and energy and protein intake and to adjust the dietary plan if needed. If a participant is readmitted within 16 weeks of discharge, they are offered dietary counseling during rehospitalization.

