#### Training of staff performing the interventions

All clinical pharmacists are educated and certified by The Capital Region Pharmacy, Herlev, Denmark, to perform medication reconciliation and medication reviews. All clinical pharmacists are provided 1 h of instruction about the intervention by CT, [name], or the primary investigator [name]. Additional instruction may be provided by [name] as needed during the trial.

Both hospital- and community-based dieticians are provided one hour of instruction about the intervention by the primary investigators, [name], or [name]. This instruction reviews standardized procedures for data collection and dietary interventions and may be repeated if deemed necessary. Hospital-based dieticians are also provided supervised training in dietary interventions by [name], [name], or already trained dieticians until deemed ready to perform the intervention unsupervised. Additional instruction may be provided by [name] or [name] as needed during the trial.

Both hospital- and community-based occupational therapists and physiotherapists are provided 1 h of instruction about the intervention by primary investigators [name] or [name]. This instruction reviews standardized procedures for data collection and therapy interventions and may be repeated on an individual basis upon request.

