Underutilization of medication	The Assessment Of Underutilization (AOU) index identifies omitted medication prescribing despite being indicated [98]. The evaluation requires a full medication list as well as a list of established medical conditions to apply one of three ratings for each condition: (A) no omission, (B) marginal omission, or (C) omission of an indicated medication without contraindication [94].	t_1_, t_2_, t_3_
Pharmacogenetic	DNA material is collected by a buccal swab. The genetic test involves variations in 14 genes and copy variants responsible for drug transport and metabolism of more than 140 commonly prescribed medications. The included genes are Cytochrome P450 (CYP) 1A2, 2B6, 2C19, 2C8, 2C9, 2D6, 3A4, 3A5, Dihydro-pyrimidine Dehydrogenase, Opioid Receptor Mu 1, Solute Carrier Organic Anion Transporter Family Member 1B1 (SLCO1B1), UDP glucuronosyltransferase family 1 member A1, UDP-glucuronosyltransferase 2B15, and Vitamin K epOxide Reductase Complex subunit 1 [99]. After genomic data translation, a personalized evidence-based report is generated based on recommendations from the Food and Drug Administration drug labels, PharmGKB and Clinical Pharmacogenetics Implementation Consortium guidelines [100, 101]. The Pillcheck software (GeneYouln Inc., Toronto/Ontario, Canada) is used for the categorization of metabolic status classes linked to evidence-based recommendations for drug prescribing, and for identifying medications that may cause reduced clinical efficacy or significant drug reactions at standard starting doses [26].	t_1_
Dietary intake	Macronutrient intake is assessed based on validated dietary records or 24-h recalls and calculated with the software VITAKOST (VITAKOST ApS, Kolding, Denmark) [74]. During hospitalization, daily dietary records are kept by the participant and validated by a dietician (only two days for participants in the control group). At follow-up visits in weeks 8 and 16, a 3-day dietary record is validated by a dietician using household measures and photo material [102] to estimate portion sizes. In case of missing dietary records, a 24-recall [73] is performed instead, which also is validated by a dietician using household measures and photo material [102].	During hospitalization , t_2_, t_3_

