### Blinding

The nature of the intervention does not allow blinding of participants or personnel performing the intervention. However, the outcome assessor is blinded to the result of the randomization throughout the trial, and all data analysis is performed blinded.

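### In-hospital energy and protein intake is a confirmative outcome validated by unblinded intervention staff, so the unqualified claim of blinded outcome assessment is wrong for this measure

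*Protocol article*

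**What the plan says.** Table 1 of the protocol article puts energy and protein intake under the confirmative outcomes, collected during admission, at 8 weeks (t2) and at 16 weeks (t3). Table 2 does the same under dietary intake. The Aims section names it among the secondary comparisons of MULTI-NUT-MED with standard care.

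For the intervention arm in hospital, the section During hospitalization says that "the research dietitian creates a dietary plan in collaboration with the participant for the participant to follow during hospitalization". It continues: "Daily dietary intake is recorded in a food diary by the participant and validated by the research dietician the following day". Gaps are filled by the same role: "If a food diary is incomplete, then the research dietician performs a 24-h dietary recall". If recorded intake falls short of requirements, the next day's plan is changed.

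Table 2 uses these in-hospital diaries as the outcome instrument. They are kept daily, but for only two days in the control group. For weeks 8 and 16 it says that "a 3-day dietary record is validated by a dietician using household measures and photo material".

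On blinding, the section Allocation concealment mechanisms and implementation labels intervention staff as unblinded and the person who recruits and collects data as blinded. The Blinding section adds that "the outcome assessor is blinded to the result of the randomization throughout the trial". It names no exception.

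After discharge, counseling is given by community dieticians, "or by hospital-based research dieticians if community-based dieticians are not available". The schedule reads: "Participants are offered 1-h home visits by the community-based dietician at 1, 2, 4, and 8 weeks after discharge".

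**The concern.** Checking a food diary and reconstructing missing entries by recall call for judgment. In hospital, the person making that judgment wrote the plan, knows the arm and is working toward the intake target against which the diary is read. If this affects the recorded values, the likelier direction is higher intake in the intervention arm. A reader who relies on the Blinding section would nevertheless take the in-hospital comparison as blinded.

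Timing raises a second, smaller question. At 8 weeks the intervention arm is offered a counseling visit that itself looks at weight and intake, and the outcome record is due at the same nominal time. Counseling close to the 3-day record could produce a short-lived response, and only in the arm that receives counseling.

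**Working it through.** No figure is involved, so the check is to set the sections side by side.

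**Hospital phase**

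1. *Is it an outcome?* Yes. Tables 1 and 2 both list intake as confirmative, with a measurement during admission.
2. *Are the plan's diaries the outcome data?* Yes. Table 2 takes the outcome from the daily in-hospital records, which are those described under During hospitalization.
3. *Who validates them in the intervention arm?* The research dietician, who also sets the plan and does the recall.
4. *Is that role blinded?* No. Setting and adjusting the plan is delivery of the intervention, and the allocation section calls such staff unblinded. The text identifies a role and not an individual, but that is enough: any research dietician who delivers the plan is unblinded.
5. *Could another validator be blinded to these records?* Hardly. Recording is daily in one arm and two days in the other, so the length of the record can reveal the arm. Under Standard care, one protein supplement is offered only to the intervention group, so it can appear in the diaries of one arm only.
6. *Does the Blinding section allow for this?* No.

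The steps cannot all stand together with an unqualified claim that outcome assessment is blinded. Who validates the two control days is not stated beyond a dietician. That does not rescue the claim, because the contradiction already holds in the intervention arm.

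**Weeks 8 and 16**

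1. Table 2 says only that a dietician validates the record.
2. Research dieticians may counsel after discharge, but only as a fallback.
3. The training section says of dieticians that "This instruction reviews standardized procedures for data collection and dietary interventions". Its subject is staff who deliver the intervention, and their home visits include an evaluation of weight and intake. Data collection there may mean no more than that.
4. Data collection methods describes separate supervised training of assessors, and the allocation section calls data collectors blinded.

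No section says that the counseling dietician validates the outcome record, and none says that this is ruled out. Unblinded validation at follow-up is therefore possible but not shown.

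**Timing**

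| | Scheduled dietician visit | Outcome record |
|---|---|---|
| Week 8 | yes, last of four | yes (t2) |
| Week 16 | none | yes (t3) |

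The two coincide nominally at week 8, with no order stated. Week 16 falls 16 − 8 = 8 weeks after the last scheduled dietician visit and does not have this overlap.

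**The case against.** The strongest reply is that the contradiction is confined to one phase of one secondary measure, and that anything beyond it is an argument from silence in a condensed article. Much of this stands.

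- A reader might infer that intake is assessed unblinded at every time point. The document does not support that: for follow-up it describes blinded, separately trained assessors and never gives the outcome record to the counselor.
- A reader might also infer that the 3-day record straddles the week-8 counseling visit. Only the nominal times coincide. The visit is also part of the intervention, so a response to it is partly treatment effect. The order of visits within a week is a detail that an article may leave to the full protocol.
- A reader might want to turn the problem into an inflated false-positive rate. That would need an SD for intake, a size for the assessor effect and the number analyzed in hospital, none of which is given. The Statistical methods section also says that the analysis of the additional confirmative outcomes is adjusted for multiple testing, so a plain 5% test is not the reference.
- Intake is recorded by participants who cannot be blinded. A blinded validator would leave their own reporting bias in place.
- The Discussion already concedes performance bias and unequal staff attention. It does not mention unblinded assessment of intake, so this answers only part of the point.

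None of this removes the conflict in hospital. There the article states who validates the record, and it is not a blinded person.

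**Conclusion.** The point holds for in-hospital intake. The Blinding section is wrong for that measure, and the unequal recording between arms means that a change of validator alone would not make it right. A between-group difference in in-hospital intake shows how the intervention was delivered and recorded; it should not be presented as a blinded confirmative result.

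At weeks 8 and 16 the right description is not explicitly safeguarded, rather than unblinded. The overlap at week 8 is an unresolved scheduling question, and week 16 is free of it.

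The size of any bias cannot be derived from the document. Its direction, toward the intervention, is a reasonable expectation and not a demonstrated fact. None of the three primary outcomes and none of the sample sizes is affected. The conclusion rests on one reading: that the in-hospital diaries in Table 2 are those described under During hospitalization. The wording of the two sections supports this.

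**What to change.** 1. Reconcile the sections During hospitalization, Table 2 (dietary intake), Allocation concealment mechanisms and implementation, and Blinding. Except in-hospital intake from the blinding statement, and report it as an unblinded process measure of the intervention instead of a confirmative between-group outcome. This costs only wording and can be done at any time before analysis.
2. Where follow-up is still open, have the 8- and 16-week records validated by a dietician already in the trial who has not counseled that participant and does not know the arm, and say so in Table 2.
3. Where follow-up is still open, complete the week-8 record before the week-8 counseling visit. The content of the counseling does not change.

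Items 2 and 3 make scheduling less flexible. That is a real cost, since the article itself plans for staff shortages and for community dieticians being unavailable. They may also come too late. Recruitment began on 15 October 2018 and was expected to take 100 weeks, which runs to about mid-September 2020; 16 weeks more reaches about early January 2021, before publication in September 2021. The article does not say whether that schedule held. If follow-up is closed, state who validated the records at each visit and whether they knew the arm, and make item 1 the change.

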##### After discharge

Prior to discharge, a dietary plan for the first week after discharge is created based on the participant’s food preferences, nutritional needs (evaluated by the Nordic Nutrition Recommendations [75] with an optional stress factor), ability to chew (pain in their mouth, difficulties chewing) and swallow (evaluated by the EAT-10 score [71, 72] and an occupational therapist), and limitations in grocery shopping, cooking or eating (evaluated by the Functional Recovery Score (FRS) [76]). If ONS is a part of the dietary plan after discharge, then the participant is provided with an ONS prescription, which can be filled at the pharmacy with a 60% price reduction. At discharge, the dietary plan is provided to both the participant and community-based dietician.

Participants are offered 1-h home visits by the community-based dietician at 1, 2, 4, and 8 weeks after discharge to evaluate changes in body weight and energy and protein intake and to adjust the dietary plan if needed. If a participant is readmitted within 16 weeks of discharge, they are offered dietary counseling during rehospitalization.

##### Occupational therapy—dysphagia

Participants with an EAT-10 score [71, 72] ≥3 at baseline are offered an evaluation by a hospital-based occupational therapist to identify the presence of dysphagia. If the participant is discharged prior to the hospital-based evaluation, then a community-based occupational therapist performs the evaluation after discharge.

If the initial evaluation of dysphagia reveals areas for potential treatment, then an intervention to improve and secure swallowing safety and efficiency is initiated. Both the evaluation and treatment are performed according to the principle of Facial Oral Tract Therapy (F.O.T.T.®) and follow prespecified algorithms [77]. Any required modifications to food and beverage consistency are coordinated with the research dietician during hospitalization and communicated to community-based staff performing the intervention after discharge. If any additional interventions for dysphagia are still required at the time of discharge, then the participant is offered home visits by a community-based occupational therapist as needed for 2 h per week for 16 weeks after discharge. All evaluation results and treatment plans are communicated to the community-based occupational therapist upon discharge. The intervention is terminated when an individualized goal of intervention is reached or after 16 weeks.

